### Sample size calculations

Formal sample size calculations were conducted for the DIALOG+ RCTs in Uganda and Colombia in order to detect a medium effect size of 0.5, setting power at 80% for 5% significance. The total number of patients required is 64 per group (*n* = 128). After accounting for clustering of patients treated by the same clinician, based on an Intra-Cluster-Coefficient of 0.01 as observed within the DIALOG+ trial in the UK [28], a conservative design effect of 1.04, and allowing for a drop-out rate of 17%, a total of 168 patients will need to be recruited to give an analysable sample of 140 (70 per group).

Estimates for exploratory randomised controlled trials vary, but it has been suggested that a minimum of 30 participants per arm are required [29]. Therefore in Bosnia-Herzegovina, the sample size for all RCTs include 36 per arm, to allow for a 20% drop out rate which has been demonstrated in previous research with individuals with psychosis [30].

For all other controlled and non-controlled trials, we plan a sample size of 30 participants per arm or in total respectively. Central limit theory suggests 30 as a minimum sample size to enable meaningful parameter estimates [31, 32].

The plan to have larger studies on DIALOG+ than on family involvement and volunteer support reflects a particular interest of stakeholders in each country who felt that DIALOG+ may play an important role in the further development and establishment of community mental health care in the participating countries.

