## Methods

### Interventions and study designs

The research conducted by the Group will test three aforementioned interventions - making patient-clinician meetings therapeutically effective through DIALOG+, family involvement in multi-family group meetings, and support for patients in befriending schemes with volunteers. Each intervention is tested in each country, i.e. there are nine studies in total. The study designs include non-controlled trials, non-randomised controlled trials and smaller and larger randomised controlled trials (RCTs). The main characteristics of the nine studies are summarised in Table 1, indicating core consistencies and differences in study designs across the three LMICs.

**Table 1 Tab1:** Main characteristics of the nine studies that will be conducted in Bosnia-Herzegovina, Colombia and Uganda

	Bosnia-Herzegovina	Colombia	Uganda
DIALOG+	Cluster RCT, 72 patients with depression and anxiety, 14 clinicians, Control group = TAU	Cluster RCT, 168 patients with SMI, 14 clinicians, Control group = TAU	Cluster RCT, 168 patients with MNS, 14 clinicians, Active control group
Family Involvement	RCT, 72 patients with SMI, 36–72 family members/friends, 6–12 clinicians, Control group = TAU	Non-controlled trial, 30 patients with SMI, 30–60 family members/friends, 6–12 clinicians, No control group	Controlled trial, 30 patients with SMI, 30–60 family members/friends, 6–12 clinicians, Control site
Volunteer Support	RCT, 72 patients with SMI, 36 Volunteers, Control group = TAU	Non-controlled trial, 30 patients with SMI, 20 volunteers, No control group	Controlled trial, 30 patients with SMI, 10 volunteers, Control Site

*Abbreviations: RCT* Randomised controlled trial, *SMI* Severe mental illness, *MNS* Mental, neurological and substance misuse disorders, *TAU* Treatment as usual

For each intervention (described below) there is some evidence for effectiveness from HICs, although that evidence is not always conclusive and does not necessarily apply to the precise form of the intervention as used in this research. Yet, all interventions can refer to theories for why they might be beneficial to patients and have been found by local stakeholders in each country to be relevant for the given context.

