## Discussion

The approach of the research group to establish a partnership across countries on three continents and explore resource-oriented interventions for community mental health care for people with SMI has led to nine separate study protocols. The content and design of the studies were developed in workshops, consultations and discussion groups at all sites. In each LMIC, each considered intervention was discussed in depth and in partnership with local stakeholders considering the local context, healthcare priorities, practicalities and logistics of conducting the research studies, as well as potential study sites, participants and study designs. Workshop attendees included different groups of mental health professionals, researchers, government officials and representatives, volunteers, peer support workers, representatives from patient and family organisations, non-government organisations and student organisations. These events and regular on-going communication among all partners led to protocols for the three types of resource-oriented interventions and for studies testing them.

The study designs which are non-controlled or non-randomised may provide limited conclusions on effectiveness whilst the exploratory RCTs have relatively small sample sizes providing limited statistical power for detecting effects. However, we believe they will provide valuable insight into the feasibility and acceptability of such interventions in the relevant contexts.

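### Minor: the 36 per arm in the three Bosnia-Herzegovina RCTs covers 16.7% drop-out, not the stated 20%, so about 29 rather than 30 per arm are expected to remain

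*Protocol article*

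**What the plan says.** In the Sample size calculations section, the basis for the Bosnia-Herzegovina trials is a rule of thumb for exploratory RCTs: "it has been suggested that a minimum of 30 participants per arm are required". The next sentence draws the consequence that "in Bosnia-Herzegovina, the sample size for all RCTs include 36 per arm, to allow for a 20% drop out rate", and attributes the 20% to earlier research in people with psychosis.

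Table 1 (Interventions and study designs) shows which trials this covers. Each has 72 patients in total:

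- DIALOG+: "Cluster RCT, 72 patients with depression and anxiety, 14 clinicians, Control group = TAU"
- Family Involvement: "RCT, 72 patients with SMI, 36–72 family members/friends, 6–12 clinicians, Control group = TAU"
- Volunteer Support: "RCT, 72 patients with SMI, 36 Volunteers, Control group = TAU"

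The paragraph just before, on the DIALOG+ trials in Uganda and Colombia, handles drop-out as follows: "allowing for a drop-out rate of 17%, a total of 168 patients will need to be recruited to give an analysable sample of 140".

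**The concern.** The sentence links a minimum of 30 to a recruitment figure of 36 through an allowance for drop-out. That link makes sense only if 30 is the number meant to remain after losses; if 30 were the number to recruit, no allowance would be needed. On that reading the three numbers (30, 36, 20%) should agree, and they do not.

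The rule of 30 per arm is the only size justification offered for these three trials, since no effect size, power or precision is given for them. A reader will take it that 30 per arm are expected at the end, when the stated assumption gives slightly fewer. What is at stake is the accuracy of a stated property of the design.

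**Working it through.** **Inputs, all from the article**

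- Suggested minimum per arm: 30 (Sample size calculations)
- Recruited per arm: 36, with drop-out d = 20% (same section)
- Total per trial: 72 in each of the three Bosnia-Herzegovina RCTs (Table 1), which matches 2 × 36
- Comparison: 168 recruited, 17% drop-out, 140 analysable, for Uganda and Colombia (Sample size calculations)

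**1. Reproduce the stated figure.** Multiplying the target by (1 + d) gives 30 × 1.20 = 36, exactly the stated number. So the 20% was applied as a mark-up on 30.

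**2. Apply 20% drop-out to those recruited.**

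- Per arm: 36 × (1 − 0.20) = 28.8
- Per trial: 72 × 0.80 = 57.6
- Shortfall: 30 − 28.8 = 1.2 per arm, or 60 − 57.6 = 2.4 per trial

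**3. Number needed to keep 30 at 20% drop-out.** n/(1 − d) = 30/0.80 = 37.5, rounded up to 38 per arm (76 in total).

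**4. Drop-out that 36 per arm does cover.** 1 − 30/36 = 16.7%.

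**5. Compare with the neighbouring paragraph.** For Uganda and Colombia, 168 × 0.83 = 139.4, stated as 140. Drop-out there is a share of those recruited. The ratio of recruited to analysable is 168/140 = 1.2, the same as 36/30 = 1.2. The same multiplier is therefore labelled 17% in one paragraph and 20% in the next. The 17% label is right to rounding (1 − 140/168 = 16.7%); the 20% label is not.

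**6. Illustration of chance variation (assumption: each patient is retained independently with probability 0.80).**

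- 36 recruited: the chance that one arm keeps at least 30 is 0.40; for both arms it is 0.40 × 0.40 = 0.16
- 38 recruited: the chance for one arm is 0.66

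These probabilities only give scale. Steps 1 to 5 do not depend on the independence assumption.

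**The case against.** The strongest reply is that this hardly matters. The gap is 1.2 patients per arm. The section introduces the 30 as one suggestion among varying estimates, and no significance level, power or effect size depends on it. The Discussion says that "the exploratory RCTs have relatively small sample sizes providing limited statistical power for detecting effects" and places the value of these studies in feasibility and acceptability. At the 17% drop-out used for the other DIALOG+ trials, 36 per arm would keep 36 × 0.83 = 29.9, so the dispute is between 20% and about 17%. All of this stands, and it limits the point to a minor correction.

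It could also be said that the article never calls the 30 analysable. That is literally true, but it leaves the allowance for drop-out without a purpose. Nor can the 20% be defended as a different convention, because the preceding paragraph counts drop-out as a share of those recruited.

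Three stronger readings are tempting, and the document does not support them:

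- **The three trials will miss their target.** 28.8 is an expectation. Under the independence assumption each arm still has about a 40% chance of keeping 30 or more.
- **The DIALOG+ trial in Bosnia-Herzegovina is further undersized because it is clustered by clinician.** The rule of thumb carries no stated precision for clustering to erode. The only intra-cluster coefficient in the article, 0.01, comes from the UK DIALOG+ trial. If borrowed, it gives 57.6/14 = 4.1 patients per clinician, a design effect of 1 + 3.1 × 0.01 = 1.03, and 28.8/1.03, or about 28 per arm. That is a change of less than one patient, resting on an untested assumption.
- **The 20% is wrong for DIALOG+ because it comes from psychosis.** The other two trials enrol ICD-10 F20–29, so the source fits them. For depression and anxiety the article gives no other rate, so neither the direction nor the size of any error can be stated.

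**Conclusion.** The point holds as a minor error, wrong as written. It applies equally to all three Bosnia-Herzegovina RCTs. The stated 36 per arm is too small for the drop-out it is said to cover, by 2 recruited patients per arm (36 against 38). Equivalently, the drop-out it covers is overstated by about 3 percentage points (20% against 16.7%).

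The conclusion rests on one interpretive step, that 30 is the number intended after drop-out, and otherwise on the article's own figures. It does not imply a loss of stated power, since none is stated, and it gives no reason to change the design or the analysis of these trials.

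**What to change.** Keep 72 patients per trial and correct the sentence in the Sample size calculations section so that the numbers agree. Suggested wording:

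> 36 per arm is expected to give about 29 analysable per arm at 20% drop-out (30 per arm at up to 16.7% drop-out).

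This costs one sentence and makes the stated position slightly less favourable. No extra patients and no change to design or analysis are needed. If the sponsor prefers to hold to 30 per arm at 20% drop-out, the arithmetic requires 38 per arm, i.e. 4 more patients in each trial (76 against 72). For exploratory trials sized by a rule of thumb, the restatement is enough.

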#### DIALOG+

DIALOG+ has been developed to turn routine meetings between a patient and mental health professional into a therapeutically effective intervention. It is based on quality of life research, concepts of patient-centred communication, developments in information technology, and components of solution-focused therapy. Supported by an App using a tablet computer, it delivers assessment, planning, intervention and evaluation in one procedure.

In the meeting with the mental health professional, patients rate their satisfaction with eight quality of life domains, and three treatment domains. The ratings are summarised on-screen, allowing for comparisons with ratings from any previous meeting. Patients can then decide which life and/or treatment domains they would like to discuss in the current meeting. Each selected life domain or treatment domain is addressed in a four-step solution-focused approach. The four steps are: 1) understanding (Why is the patient dissatisfied? What is nevertheless working well?); 2) looking forward (What is the best case scenario? What is the smallest step forward?); 3) exploring options (What can the patient, the mental health professional and others do?); and finally 4) agreeing on actions (What should be done between now and the next meeting?). The agreed actions are briefly documented and revisited at the beginning of the next meeting.

In an RCT in London, DIALOG+ was compared with an active control condition and was shown to lead to better quality of life, lower symptom levels, more favourable objective social situation and reduced health care costs for patients with schizophrenia [4–6].

DIALOG+ will be tested in three cluster randomised controlled trials, in which mental health professionals and their patients, i.e. clusters, are randomly allocated either to the experimental or the control group. This design will prevent potential contamination effects between the groups and ensure that no professional who is trained in DIALOG+ administers it to a patient in the control group. DIALOG+ will be delivered by mental health professionals, once per month over a period of 6 months, as part of usual routine clinical meetings.

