In each country, DIALOG+ will be administered to outpatients with SMI, diagnosed using International Classification of Diseases, Tenth Revision (ICD-10) criteria [7] by mental health professionals but with slight variations in the diagnosis and patient numbers based on the priorities expressed by national stakeholders and reflecting differences in national health and social care systems.

In Uganda, 168 patients with SMI defined as having been diagnosed with psychosis, bipolar, and/or mood affective disorders, (ICD-10 F20–29, F30-F39), epilepsy and/or comorbid substance abuse and 14 mental health professionals including nurses, social workers, psychiatric clinical officers, psychologists and psychiatrists will be part of the trial. The RCT in Uganda will comprise of an active control arm. Patients in the control group will also receive an intervention on a tablet, where they will be asked to complete the DIALOG scale which includes only satisfaction ratings, with minimal input from clinicians. This will be done at the end of their routine sessions so that the ratings will not influence the communication during the meeting.

In Colombia, 168 patients with SMI defined as having been diagnosed with psychosis, bipolar, and/or mood affective disorders (ICD-10 F20–29, F31, F32) will be included and all 14 mental health professionals will be qualified psychiatrists or psychiatric residents.

In Bosnia, a RCT will be conducted with 72 patients with severe depression and anxiety (ICD-10 F30-F39, F40-F49, excluding bipolar disorder) and 14 mental health professionals who will be qualified psychiatrists, psychologists or psychiatric residents.

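### The cluster-randomised DIALOG+ trial in Bosnia-Herzegovina is sized at 36 per arm with no clustering allowance, and at the stated 20% loss the 36 does not keep the plan's own minimum of 30

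*Protocol article*

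**What the plan says.** In the DIALOG+ section of the protocol article, all three DIALOG+ trials are cluster trials in which "mental health professionals and their patients, i.e. clusters, are randomly allocated either to the experimental or the control group". Table 1 (Interventions and study designs) lists the trial in Bosnia-Herzegovina as "Cluster RCT, 72 patients with depression and anxiety, 14 clinicians, Control group = TAU".

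Sample size calculations then uses two different bases.

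- **Uganda and Colombia.** A formal calculation, adjusted "After accounting for clustering of patients treated by the same clinician", with an ICC of 0.01, a design effect of 1.04 and 17% drop-out.
- **Bosnia-Herzegovina.** A rule of thumb for exploratory trials: "it has been suggested that a minimum of 30 participants per arm are required". From this, "in Bosnia-Herzegovina, the sample size for all RCTs include 36 per arm, to allow for a 20% drop out rate". The rate is described as a "20% drop out rate which has been demonstrated in previous research with individuals with psychosis".

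The DIALOG+ trial in Bosnia-Herzegovina enrols "72 patients with severe depression and anxiety". The other two trials there, family involvement and volunteer support, enrol ICD-10 F20–29 and also have 72 patients each. The section ends by saying that the plan for "larger studies on DIALOG+ than on family involvement and volunteer support reflects a particular interest of stakeholders in each country".

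**The concern.** One section treats the same kind of design, with the same number of clinicians, in two ways and gives no reason. Two trials with 14 randomised clinicians are inflated for clustering. The third has 14 randomised clinicians too, but takes its size from a per-arm rule shared with two individually randomised trials. A reader would conclude that 36 per arm rests on the same footing in all three Bosnian trials and leaves at least 30 usable patients per arm in each.

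The drop-out rate raises a second question. Its source population fits the two F20–29 trials, but not a trial in depression and anxiety.

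What is at stake is how the precision of this trial is described. No power target is involved, because none is set for the Bosnian trials.

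**Working it through.** **Inputs from the protocol article:** minimum 30 per arm; 20% drop-out; 36 per arm; 14 clinicians; ICC 0.01 and design effect 1.04 (both stated for Uganda and Colombia).

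**Assumptions added here:** 7 clinicians per arm, equal numbers of patients per clinician, and losses spread evenly over clinicians.

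**1. Reproduce the 36.** 30 × (1 + 0.20) = 36 per arm, 72 in total. This matches exactly with no further factor, so 36 contains no clustering allowance.

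**2. Apply the stated loss.** 36 × (1 − 0.20) = 28.8 per arm, 57.6 in total. To keep 30 after a 20% loss takes 30 / 0.80 = 37.5, so 38 per arm. The 36 keeps 30 only if the loss is 1 − 30/36 = 16.7%. This step applies equally to the other two Bosnian trials.

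**3. Add clustering.** With m analysed patients per clinician, design effect = 1 + (m − 1) × ICC.

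- m = 28.8 / 7 = 4.11.
- ICC 0.01: 1 + 3.11 × 0.01 = 1.031, so the effective size is 28.8 / 1.031 = 27.9 per arm.
- ICC 0.05 (assumption): 1 + 3.11 × 0.05 = 1.156, so 28.8 / 1.156 = 24.9 per arm.

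On recruited patients m = 36 / 7 = 5.14 and the design effect is 1.041, so the plan's own 1.04 would also fit this trial.

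**4. Split the gap to 30 at ICC 0.01.**

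| Source | Patients per arm |
|---|---|
| Drop-out inflation: 30 − 28.8 | 1.2 |
| Clustering: 28.8 − 27.9 | 0.9 |
| Total: 30 − 27.9 | 2.1 |

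**5. Size that would hold 30 effective.** 30 × 1.04 / 0.80 = 39 per arm, 78 in total.

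**6. Precision, if the analysis uses between-clinician degrees of freedom (14 − 2 = 12).** The 95% half-width in SD units is t × √(2 × design effect / 28.8), with ICC 0.01.

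| Case | t | Design effect | Half-width (SD) |
|---|---|---|---|
| Individual randomisation (55.6 df) | 2.004 | 1 | 0.528 |
| Design effect only | 2.004 | 1.031 | 0.536 |
| 12 df only | 2.179 | 1 | 0.574 |
| Both | 2.179 | 1.031 | 0.583 |

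The interval is about 10% wider with both (0.583 / 0.528 = 1.10). The design effect alone contributes a factor of √1.031 = 1.015. The change of t contributes 2.179 / 2.004 = 1.087.

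**7. Sensitivity to drop-out, before clustering.** 36 per arm leaves 32.4 at 10% loss, 30.6 at 15%, 27.0 at 25% and 25.2 at 30%.

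**8. Sizes across interventions (Table 1).** Bosnia-Herzegovina: 72, 72 and 72. In Uganda and Colombia DIALOG+ has 168 patients, against 30 intervention patients in each of the other studies.

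**The case against.** The strongest reply is that nothing the plan promises for this trial is broken. The section gives no effect size, power or interval width for the Bosnian trials. It calls the minimum of 30 a suggestion and says such estimates vary. The Discussion concedes that the exploratory RCTs are small and have limited power. At the plan's own ICC, clustering costs less than one effective patient per arm. All of this stands, and it limits the remedy to a restatement. It does not explain why one section adjusts two of three clinician-randomised trials, or why a size said to allow for 20% loss falls below its own minimum at that loss.

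Four stronger readings are tempting, and the documents do not support them.

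- **DIALOG+ carries the least information of the three Bosnian trials.** This is not shown. The family involvement arm meets in groups of about five to six patients, so its outcomes may be correlated within groups too. The article gives no ICC for those groups.
- **Clustering makes the interval 10% wider.** Most of that widening comes from using 12 degrees of freedom. The article does not fix that analysis; Data management and analysis defers the detail to statistical analysis plans that are not shown.
- **The 20% drop-out is wrong for this trial.** Nothing shows that it is too high or too low for depression and anxiety. It is only unsupported for them, and the article names its source openly.
- **The article states that DIALOG+ studies are larger in every country.** In the closing sentence, the words about each country attach to the stakeholders. Over the programme DIALOG+ is plainly the largest, with 72 + 168 + 168 = 408 patients. The sentence is loose, because it does not hold within Bosnia-Herzegovina.

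**Conclusion.** The point holds as an inconsistency in how the sample size is justified. The Bosnian DIALOG+ trial is cluster-randomised but has no clustering allowance, while the same section makes one for the same design elsewhere. Its 36 per arm yields 28.8 after the stated loss and about 27.9 effective per arm at ICC 0.01, so the stated minimum of 30 is not met. More than half of the shortfall (1.2 of 2.1) comes from multiplying by 1.20 instead of dividing by 0.80. Clustering accounts for about 0.9.

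The clustering part becomes material only at a higher ICC, such as 24.9 effective per arm at 0.05, and that value is an assumption. The half-width of about 0.58 SD against 0.53 SD depends on an analysis with 12 between-clinician degrees of freedom. All figures assume seven clinicians per arm with equal numbers of patients.

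The drop-out source and the sentence about larger DIALOG+ studies are secondary matters of wording. The trial remains acceptable as an exploratory study of its stated size.

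**What to change.** In Sample size calculations:

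1. Give the Bosnian DIALOG+ trial its own sentence. State that it is randomised by clinician, that the design effect at ICC 0.01 is about 1.03 on analysed patients (1.04 on recruited), and that 36 per arm is expected to leave about 28 effective patients per arm after 20% loss. Show ICC 0.05 as a labelled assumption (about 25). Say that holding 30 would take 39 per arm and that recruitment stays at 36.
2. Say that precision falls further if the analysis uses the 12 between-clinician degrees of freedom: half-width about 0.58 SD, against 0.53 SD under individual randomisation.
3. For all Bosnian trials, correct the implication that 36 keeps 30 at 20% loss; it leaves 28.8.
4. Mark the 20% drop-out in the DIALOG+ trial as an assumption borrowed from psychosis research.
5. Make clear that the sentence about larger DIALOG+ studies applies to Uganda and Colombia.

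The cost is a few reworded sentences and a slightly less favourable stated figure. No extra patients, clinicians or assessments are needed.
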